### *Research protocol– [name]*

A log will be kept of all infants discharged to home from the unit i.e. to evaluate drop-out rate and biases (Appendix A). The log includes the patient's gestational age, birth weight, diagnosis, type of feeding at discharge, and the length of hospital stay. If there is missing information in the log, it is completed with the information from the medical records. A log is also kept to follow the units' restrictions related to Covid-19 and concerning family visitation and participation policies (Appendix B/C).

## **Methods**

### Methods to assess the fidelity

The fidelity is analysed by tracking the participants' behaviour in the e-learning module by analytic softwares, such as Google Analytics, Hotjar and Vimeo. The participants are informed about this and they are asked for their written consent and agreement when entering the module for the first time. Furthermore, a log is kept about the practices the mentors are carrying out with their colleagues in the units (Appendix D).

### Methods to assess the impact of the intervention on staff

#### *Background questionnaire*

A questionnaire is used to collect background information of staff members (Appendix 1).

#### *Collaboration competence questionnaire*

A questionnaire is used to assess the collaboration competence of the staff at the beginning of the intervention, in the middle of the implementation and in the end. The questionnaire is specifically created to assess competencies that are relevant for the Close Collaboration with Parents training program. The questionnaire includes 21 questions that are evaluated with scale from 1 to 10 (1=not competent at all, 10=extremely competent). If the question does not ably the daily work role of the professional option "Doesn't belong to my role" can be used. (Appendix 2)

#### *The reflective thinking*

The level of reflective thinking of the staff is measured using the Reflective Thinking Measure (Appendix 3). The 16-question measure determines whether an individual engages in reflective thinking and to what extent s/he does that. The questions are answered with options varying from strongly agree, which is scored as 5, through to strongly disagree, which is scored as 1. Scores range from 16 to 80, with 80 indicating the highest possible level of reflection. The 16 questions form four factors: 1) Habitual Actions, 2) Understanding, 3) Reflection and 4) Critical reflection. The structural validity of the scale has been tested with health care professionals and it has shown to be good.

The level of reflective thinking is also assessed with questions related to a fictitious case (Appendix 4). The case represents so called 'critical incident' that the staff is asked to describe from three perspectives: (a) how they would normally act in a similar situation in their unit; (b) a general meaning and reflect how

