#### The specific research questions are as follows:

1. What is the achieved level of fidelity in the implementation process of the intervention in the Estonian context?
2. Does the intervention promote immediate changes in the staff's collaboration competence, perception of the FCC care provision, and reflective thinking?
3. Does the intervention have a significant positive effect on the FCC practices of the units?
4. Does the intervention have a significant positive effect on parenting self-efficacy, parental mood and parents' readiness for discharge at the time of hospital discharge?
5. If the answers to questions 2, 3, and 4 are positive, we will then seek to answer whether the potential impact mechanisms mediate the improvements in unit FCC practices, parental self-efficacy, mood and readiness for discharge.

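### The Reflective Thinking total scores agreement with Habitual Actions items as more reflection, so a total of 80 cannot mean the highest level of reflection.

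*Protocol*

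**What the plan says.** The Protocol, under *The reflective thinking* (staff methods), fixes three things about the questionnaire.

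- **Item scoring.** "The questions are answered with options varying from strongly agree, which is scored as 5, through to strongly disagree, which is scored as 1". This is one rule for all questions; no item is exempted or reversed.
- **Total and its meaning.** "Scores range from 16 to 80, with 80 indicating the highest possible level of reflection".
- **Content.** "The 16 questions form four factors: 1) Habitual Actions, 2) Understanding, 3) Reflection and 4) Critical reflection".

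The same section adds a second measure of reflective thinking, a fictitious critical-incident case answered from three perspectives. Research question 2 asks: "Does the intervention promote immediate changes in the staff's collaboration competence, perception of the FCC care provision, and reflective thinking". Research question 5, on mediation, is taken up only if questions 2, 3 and 4 are answered positively. The protocol does not say which reflective-thinking score is used for either question.

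**The concern.** The factor names set Habitual Actions apart from Reflection and Critical reflection. It need not be their exact opposite. It is enough that stronger agreement with habit items is not more reflection. Under the stated rule, each such agreement nevertheless raises a total that the protocol reads as level of reflection.

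Reflective thinking is one of three staff mechanisms in question 2, and testing the impact-mechanisms model is the study's specific goal. If the 16-80 total carries this construct, staff who become more reflective and less habit-bound have part of their change removed by the scoring. That could count against a positive answer to question 2, which is a condition for question 5, and could weaken the mediator itself.

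**Working it through.** **Inputs from the Protocol, *The reflective thinking*:** 16 items; item scores 1 to 5, with strongly agree = 5; four factors. **Assumption:** the number of items per factor is not stated, so 16 / 4 = 4 each is assumed, with 3 and 5 habit items shown as a range.

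**Step 1. Reproduce the stated range.** Minimum 16 × 1 = 16; maximum 16 × 5 = 80. This agrees with the protocol. A reversed item (6 minus score) also runs from 1 to 5, so the range is the same with or without reversal. The range therefore does not show whether habit items are reversed.

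**Step 2. Who scores 80?** With *h* habit items, take a respondent who strongly disagrees with all of them and strongly agrees with everything else. The total under the stated rule is *h* × 1 + (16 − *h*) × 5 = 80 − 4*h*. With habit items reversed, this respondent scores 80. A respondent who strongly agrees with everything scores 80 under the stated rule and 80 − 4*h* with reversal.

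| Habit items | Least habit, maximum on the rest: stated rule | Same respondent: habit reversed | Agrees with everything: stated rule | Same respondent: habit reversed |
|---|---|---|---|---|
| 3 | 68 | 80 | 80 | 68 |
| 4 | 64 | 80 | 80 | 64 |
| 5 | 60 | 80 | 80 | 60 |

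Reversal swaps the two respondents. The stated meaning of 80 is right only for the reversed score.

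**Step 3. Effect on a change score (four items per factor).** Let ΔH, ΔU, ΔR and ΔC be the summed changes in Habitual Actions, Understanding, Reflection and Critical reflection. The stated rule gives ΔH + ΔU + ΔR + ΔC. Reversal gives −ΔH + ΔU + ΔR + ΔC. A shift of one point per item is 4 × 1 = 4 points per factor.

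| Habit falls by 4 and … | Stated rule | Habit reversed |
|---|---|---|
| Reflection rises by 4 | −4 + 4 = 0 | 4 + 4 = +8 |
| Reflection and Critical reflection each rise by 4 | −4 + 8 = +4 | 4 + 8 = +12 |
| Understanding, Reflection and Critical reflection each rise by 4 | −4 + 12 = +8 | 4 + 12 = +16 |

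In general, a fall of *d* summed points in habit takes *d* points off the gain on the other three factors, and puts the total 2*d* points below the reversed score. If habit does not change, nothing is lost.

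**The case against.** The strongest reply is that the section describes an instrument and does not choose an analysis. The total is not named as the outcome for question 2 or as the mediator for question 5. The four factors are listed directly after the range, which is compatible with factor-level analysis, and that choice is commonly left to a statistical analysis plan. This stands as a limit on the consequence: the loss arises only if the total is used. It does not rescue the scoring description, because the item rule and the meaning of 80 are stated in the protocol itself.

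A second reply is that Appendix 3 is not shown and may hold a reverse key. It may, and the sentence about 80 would then be true. But such a key would contradict the single scoring rule in the main text, which would still need correcting.

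Two stronger readings are tempting.

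- A reader might infer that the training effect cancels out. The documents do not support that as a general result: it needs a fall in habit equal to the rise elsewhere, in summed points. Otherwise the effect is attenuated, by an unknown amount.
- A reader might infer that reducing habit is a declared aim, so the loss is certain. The protocol describes training through bedside practice and reflection on it, and states no aim of lowering Habitual Actions. A fall in habit is plausible but inferred.

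The critical-incident case also means that the construct does not rest on this total alone.

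**Conclusion.** The concern holds as an inconsistency in a stated scoring rule. With all 16 items scored in one direction and Habitual Actions among them, 80 is not the highest level of reflection. The least-habit, most-reflective respondent scores 64 with four habit items, and 60 to 68 with five to three. If the total is used for question 2 or question 5, a fall in habit attenuates the measured gain: 0 instead of +8, or +4 instead of +12, in the worked cases of one point per item.

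This rests on two assumptions: the number of items per factor, which is not stated, and the reading, taken from the factor names, that agreement with habit items is not reflection. The inconsistency itself needs only the second. The size of any loss in this study cannot be derived from the protocol, since it depends on which score is analysed and on how far habit changes.

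**What to change.** Choose one scoring and state it under *The reflective thinking*:

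- analyse the four factor scores separately; or
- keep a single total, but reverse-score each Habitual Actions item (6 minus item) before summing.

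If no reversal is applied, delete the statement that 80 is the highest level of reflection. In either case, state which score serves questions 2 and 5. If factor scores are used, which of them carry those questions is for the study team to decide in advance. If Appendix 3 already contains a reverse key, bring the main text into line with it.

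The cost is wording and scoring syntax. No new data are needed, because either scoring can be applied to the item-level responses.

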## Materials and Methods

### Design

A quasi-experimental before and after intervention design is used to test the effect of the intervention, where the impact mechanisms are treated as mediators of the change.

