### Data collection

The pre-intervention data is collected in spring 2021 during a four-month period when the training on unit mentors is going on, but the implementation to the unit has not begun. The data measuring the fidelity of intervention implementation will be collected between January 2021 and October 2022. The post-intervention data is collected in the shift of the years 2022 and 23 during a four-month period. (Figure 2).

| Data collection                                                                                                | 2021       | 2022                    | 2023         |
|----------------------------------------------------------------------------------------------------------------|------------|-------------------------|--------------|
| Parents’ data:
FCC, parental self efficacy, parental depression and anxiety, and discharge readiness | 2-4/21     |                         | 11/22 – 2/23 |
| Staff’s data:
Collaboration competence, reflective thinking, provision of FCC                        | 2-4/21     | After training Phase II | 11/22 – 2/23 |
| Fidelity                                                                                                | 1/21-10/22 |                         |              |
| CC Intervention                                                                                         | 1/21-8/21  | 9/21-10/22              |              |

**Figure 2.** Illustrates the timeline of the data collection.

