### *Research protocol– [name]*

the general meaning resonates with their own experience; and (c) potential new ways of acting in the situation that would provide better support for the family.

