All the data will be handled anonymously. The participants will get an ID code that is used when data is stored and analyzed. The recruitment log of the parents and staff members are used to undo the ID codes and, therefore, they are kept separately from the data files. The analytic softwares (Google Analytics, Hotjar and Vimeo) also track anonymously participants' behavior on the e-learning module's website. The personal details (password, email, etc) are not recorded and the IP addresses are anonymized by cutting out the last few digits, so only the rough geographical area of access to the e-learning module is identified. The logs and all the data will be destroyed five years after the last publication from the data.

The intervention

The Close Collaboration with Parents intervention will be carried out in the four NICUs in Estonia. The delivery of the intervention follows a structure that has been developed and fine-tuned between 2009 and 2020 when it was implemented in 14 NICUs. First, experienced nurses or doctors from the units will undergo a three-week training to become "unit mentors," and then these unit mentors will train other members of staff. The training of the units is strongly based on experiential learning utilizing bedside practices, reflection of the practices, and application of this knowledge in everyday clinical situations. Theoretical teaching, which precedes clinical bedside mentoring, will occur through a new e-learning tool. Each staff member will spend about four working days training alongside his or her routine work. The unit mentors will function as facilitators for all the staff, and they have dedicated time for this. The content of the bedside practices is guided by a manual. To support the delivery of this phase, the training

team will provide frequent remote supervision for the unit mentors and leadership. The units have committed to allocate the resources for the implementation of the intervention. The applicant will have the main responsibility for the delivery of the training. The aim is to train about 75% of the staff members in the units during the 18-month period.

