## **Finances**

The units are responsible for the following costs related to the study. At least following costs need to be considered:

- Intervention costs (training fee + salary of the mentor nurses)
- Material (printing out the informed consent forms, information and instruction for the parents and staff, diaries)
- Desk computer/laptop and Internet access available for the study period for the web questionnaire
- Cost of the ethical approval
- Cost of research staff/ nursing staff participation
- Data entry

Data analysis is centralized and paid in Finland.

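### Nothing in the visible protocol hides the collection period from whoever rates the fictitious-case answers for level of reflection

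*Protocol*

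**What the plan says.** Under The reflective thinking, in the section on staff methods, two measures are described. The first is a 16-question self-report scale with 1–5 item scoring and a total from 16 to 80. The second is added to it: "The level of reflective thinking is also assessed with questions related to a fictitious case (Appendix 4"). On the format of the answers the protocol says: "The case represents so called 'critical incident' that the staff is asked to describe from three perspectives". The perspectives are the usual way of acting, a general meaning and how it fits the respondent's own experience, and "potential new ways of acting in the situation that would provide better support for the family". No numeric scale, scoring rule or rater is given for the case.

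Figure 2 under Data collection has a staff row reading "Collaboration competence, reflective thinking, provision of FCC", with collections at 2-4/21, "After training Phase II", and 11/22–2/23.

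The Design section states: "A quasi-experimental before and after intervention design is used to test the effect of the intervention". No comparison units are described. The background text says that the research team developed the intervention. Under The intervention, within Data management, the protocol adds: "The applicant will have the main responsibility for the delivery of the training". The same part of the document gives participants ID codes for storage and analysis.

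**The concern.** The other staff and parent outcome scores come from numbers that the respondent enters, so no assessor's opinion enters them. The case is different, because a person must read text and decide how reflective it is. If that person knows whether the text was written before or after training and expects improvement, later answers may be rated higher with no change in the staff.

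With no comparison units, such a shift cannot be separated from an effect of the intervention. Research question 2 asks whether the intervention changes staff reflective thinking, and this measure is one of the two that inform it. Staff cannot be masked to their own training, but a reader of stored text can be masked to its date, at least in part.

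The timing also matters. Once a reader has rated the baseline answers knowing that they are baseline, that reader can no longer be masked for them. The decision therefore belongs to study conduct and cannot be deferred to the analysis.

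**Working it through.** The protocol gives no figure for this outcome, so there is nothing to reproduce. The check sets the relevant sections side by side.

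1. **Does the case need a reader's judgement?** The 16-question scale has stated item scores and a stated range. The case has three descriptive prompts and no scale, yet it is said to assess a level. A level can then come only from someone judging the text. That the answers are free text is inferred from the wording of the prompts; Appendix 4 is not shown.

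2. **Is it repeated across periods?** Figure 2 lists reflective thinking as a single entry at three collections. It does not separate the case from the scale, and the section on reflective thinking gives no schedule of its own. The natural reading is that both measures follow Figure 2.

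3. **Is the period hidden?** The visible protocol mentions no masking of period. The nearest safeguard is the ID code, which separates names from data. It does not remove the date or time point, and a code kept for one person across collections would also let a reader line up that person's answers.

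4. **Does the design absorb a rating shift?** No. The contrast is after versus before in the same units. If readers rate later answers higher by an amount *b* from expectation alone, the observed difference is the true change plus *b*, and nothing in the design estimates *b*.

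5. **Is there reason to expect a direction?** The team developed the intervention, reports favourable earlier results for it in the background text, and includes the applicant who has main responsibility for the training. That is a plausible source of expectation. It does not show who will rate.

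6. **Would holding the answers disrupt anything stated?** From the end of the baseline window in Figure 2 (April 2021) to the end of the final one (February 2023) is 22 months. The visible protocol names no use of baseline case ratings within that time.

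**The case against.** The best reply is that the protocol is silent here, not wrong. Appendix 4 or the cited critical-incident method may contain a scoring guide, and details of rating could be set out elsewhere. This stands as a limit on what can be claimed. It does not dispose of the point, because a scoring guide would not by itself hide the period.

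Several stronger readings are tempting, and the documents do not support them.

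- **The trainers will rate the answers.** A reader might infer this from the applicant's role together with "Data analysis is centralized and paid in Finland". That line stands under Finances and does not say who reads the case answers. Bedside training is given by unit mentors from the hospitals, with the training team supervising remotely. The protocol neither assigns the rating to a trainer nor rules it out.
- **The mediation analysis is contaminated.** Question 5 depends on positive answers to questions 2, 3 and 4, but no text says that a case rating enters the mediator model, or even that the case answers become a number. The case supplements the self-scored scale.
- **A size can be given.** On an assumed four-level rating, with 10–20% of later answers lifted by one level and an assumed SD of 0.8, the spurious shift would be 0.10 × 1 / 0.8 = 0.125 to 0.20 × 1 / 0.8 = 0.25 SD. Every input is an assumption, so this range cannot support any severity.
- **Masked rating would make the case an independent check on the scale.** It would not. Staff know that they were trained and can write the answer they were taught. Masking the reader leaves that bias in place.

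**Conclusion.** The point holds in a limited form. Narrative answers are to be judged for level of reflection, reflective thinking is scheduled in all three periods, and the visible protocol does not keep the reader from knowing the period. In a before-after design without comparison units, reader expectation could contribute to an apparent change in this one supplementary measure for question 2. The self-scored 16-question scale has no reader and is not affected by this mechanism.

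The size cannot be estimated from the documents. The conclusion assumes that the answers are free text, that the case follows the Figure 2 schedule, and that Appendix 4 contains no masking provision. It is a cheap improvement and not a flaw that undermines the study.

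**What to change.** Add to the section on reflective thinking that:

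- fictitious-case answers are held unrated until the 11/22–2/23 collection is complete;
- they are then exported under a random answer number, without date, time point, unit or staff ID;
- answers from all time points are shuffled together and rated in one batch;
- period is re-linked only after the ratings are locked;
- where the existing team allows, the reader is someone who did not deliver the training.

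The content of the answers should not be edited. Removing references to the training could remove the very reflection being rated.

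The cost is a masked export and a random ordering of text that must be read anyway. No extra reader is required, since a non-trainer is a preference and not a condition. Baseline ratings come later, by up to the 22 months shown above. Training vocabulary in later answers may partly reveal the period, and respondent bias remains. The report should therefore not present the case as an independent check on the self-rated scale.

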### *Research protocol– [name]*

the general meaning resonates with their own experience; and (c) potential new ways of acting in the situation that would provide better support for the family.

